| STATISTICAL CONSIDERATIONS: | 
Collected data will be identified only by a volunteer identification number. At the end of the study, a full analysis will be prepared according to a pre-specified statistical analysis plan. All analyses will be based on the modified intention-to-treat cohort and will analyze volunteers according to the group to which they were randomized.
 
Safety and tolerability will be addressed by examining the overall rates of adverse events and serious adverse events that might be associated with FTC/TDF daily and FTC/TDF intermittent regimens. All clinical and routine laboratory data will be included in the safety analysis. With 24 volunteers assigned to daily or intermittent FTC/TDF, observing no drug-related serious toxicity would result in an exact, two-sided, 95% confidence interval of (0.0000, 0.1425). If one drug-related SAE is observed, the exact, two-sided, 95% confidence interval would be (0.0011, 0.2112).
 
The proportion of volunteers who took at least 80% of the study medication recorded using Medication Event Monitoring System (MEMS) data will be estimated. For the intermittent group, since the dosing frequency is dependent on sexual activity, data collection using cell phone communication will be used to determine daily sexual activity in order to determine the number of expected doses. Adherence will be expressed as overall percent adherence over the study interval, longitudinal adherence by month, and for the intermittent regimen, adherence to twice weekly scheduled doses and adherence to doses during days of sexual activity. With 36 volunteers (combining active and placebo for each regimen), this study will have 51% power to detect a true adherence rate of 90% for each regimen. Power increases to 90% if the true adherence rate is 95%.
 
The proportion of volunteers assigned to FTC/TDF with detectable plasma FTC/TDF levels within 48 hours of a MEMS event will be estimated. Levels of FTC/TDF in hair samples will be evaluated for exploratory purposes only.
 
Assuming intracellular drug level has a log-normal distribution with a between subject standard deviation of 1.0 on the natural logarithm scale, this study should have about 79% power to rule-out a two-fold or greater relative decrease in the geometric mean concentration due to intermittent versus daily FTC/TDF. If the between subject standard deviation is 0.5, then there will be about 80% power to rule-out a 1.5-fold or greater decrease in the geometric mean concentration.
 
Intracellular drug levels will be correlated with adherence data for volunteers assigned to FTC/TDF for each regimen.
 
Descriptive statistics will be used to describe changes in HIV risk behaviour. Assuming condoms are used always or frequently by 60% of volunteers at baseline, this study has 85% power to detect a decrease in condom usage by treatment group (n=24) if volunteers
 |

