### **3.3.3.2 Antiretroviral drug levels to measure adherence**

Several investigators have examined antiretroviral drug levels as a measure of adherence [99-102]. The interpretation of random drug levels to most ARTs is complicated, however, because concentrations reflect drug absorption and metabolism as well as adherence to recent doses.

Drug levels for shorter half-life medications reflect only recent adherence, which may be heavily influenced by the patient improving his/her adherence just prior to a scheduled blood draw, otherwise known as “white coat compliance [103]. Drug levels in longer half-life medications such as tenofovir and emtricitabine may be less sensitive to “white coat compliance” and may better reflect long-term adherence. The half-life of tenofovir in plasma is 17 hours and levels remain detectable out to 48 hours after a single dose [43]. The half-life of intracellular tenofovir diphosphate in blood cells is estimated to be at least 60 hours [35]. Because few studies have combined both objective behavioural adherence measures and drug levels [104], the relationship between adherence and drug level, especially to longer half-life medications is largely unknown. We propose to determine to what extent intracellular tenofovir diphosphate and emtricitabine drug levels are associated with objectively measured adherence both for daily PrEP and for intermittent PrEP. Specimen collection for drug levels poses fewer logistical challenges than objective measures of adherence behaviour. Characterizing the relationships between objectively measured adherence and drug levels could provide future studies with valid and feasible approaches to better understand how adherence impacts prevention efficacy.

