##### *Intracellular drug concentrations:*

- The mean intracellular drug concentration for each group assigned to FTC/TDF

*Adherence:*

- The proportion of volunteers, who by MEMS data, took at least 80% of expected doses of the investigational product
- The proportion of volunteers assigned to FTC/TDF who have detectable drug plasma levels within 48 hours of reported use
- The relationship between intracellular drug levels and adherence in volunteers assigned to FTC/TDF

*Behavioural:*

- Reported number of steady and casual sex partners
- Frequency of unprotected vaginal intercourse
- Substance use prior to or during sex

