#### **5.2.2 Study Population**

HIV-discordant couples where the HIV-uninfected volunteer is a healthy male or female adult 18-49 years of age who is willing to undergo HIV testing, counseling and receive the HIV test results, if female use an effective method of contraception, and who, in the opinion of the principal investigator or designee, understand the study and who provide written informed consent.

For the HIV-uninfected volunteer, principal exclusion criteria include confirmed HIV-1 or HIV-2 infection; pregnancy and lactation; chronic disease; chronic hepatitis B infection; clinically significant abnormal laboratory values.

For the HIV-infected partners of the HIV-uninfected volunteer who meets study eligibility, principal inclusion criteria include planning to remain in the relationship for the duration of the study; understanding the study; and providing written informed consent. Principal exclusion criteria for HIV-infected partners is current use of antiretroviral therapy or concurrent enrolment in another HIV treatment trial.

Both members of the discordant couple will be enrolled in the study, but only the HIV-uninfected partner will be randomized to the investigational product. Approximately 72 volunteers (24 FTC/TDF daily, 24 FTC/TDF intermittent, 12 placebo daily, 12 placebo intermittent recipients) who meet all eligibility criteria will be included in the study.

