We will examine the degree of correspondence between MEMS and 30 day recall data using a linear model, taking repeated measures into account, to compare predicted adherence from MEMS and IVR/SMS with 30 day recall data. Similarly adherence from MEMS will be compared with plasma and intracellular drug levels for correspondence. We will determine if PrEP adherence declines over time by comparing median adherence each month using a linear model, testing for a non-zero slope and proportion >90% adherent using logistic regression. Finally we will describe time to PrEP discontinuation (or non-persistence), defined by >30 days without a MEMS event, with Kaplan-Meier methods. Volunteers who discontinued study treatment due to intolerance, toxicity, or pregnancy will be censored at the time of treatment discontinuation.

With 24 volunteers per treatment group, a two-sided, 0.05 level binomial test of 75% adherence will have only 29% power to detect a true adherence rate of 90%. Power increases to 66% if the true adherence rate is 95%.

If we combine the intermittent FTC/TDF and intermittent placebo groups (n=36), then a two-sided, 0.05 level binomial test of 75% adherence will have 51% power to detect a true adherence rate of 90%. Power increases to 90% if the true adherence rate is 95%. Likewise, if we combine the daily FTC/TDF and the daily placebo groups (n=36), we will have reasonable power to detect high rates of adherence.

The relationship between adherence and intracellular drug level will be evaluated in the volunteers assigned to active regimens FTC/TDF. Determining the relationship between adherence and intracellular drug levels may provide adherence estimates for future studies which do not include detailed objective adherence measures. The correlation between mean adherence execution over the prior month and intracellular drug level will be tested using Pearson's correlation coefficient. Mean drug levels in individuals with  $\geq 90\%$  adherence will be compared with those with <90% adherence using a student's T test.

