#### **14.2.5 Intracellular drug concentration**

Assuming Week 16 intracellular drug concentration has a log-normal distribution with a between subject standard deviation of 1.0 on the natural logarithm scale, this study should have about 79% power to rule-out a two-fold or greater relative decrease in the geometric mean concentration due to intermittent versus daily FTC/TDF. If the between subject standard deviation is 0.5, then there will be about 80% power to rule-out a 1.5-fold or greater decrease in the geometric mean concentration.

Pharmacokinetic (PK) modelling using plasma and intracellular drug concentrations will be performed to estimate individual PK parameters based on 2 drug levels following an observed dose, body weight, and creatinine clearance, and informed by population-PK parameter estimates. The MEMS data will be combined with the individual PK

estimates to simulate concentration-time relationships for the study. The PK-MEMS simulated concentrations will be compared to observed concentrations to evaluate plausibility of the reported dosing behaviour in comparison to that which is observed. Individual estimates of mean trough concentrations (plasma and intracellular) will be estimated. Comparisons between intermittent and daily regimen will be compared using actual and simulation-based values.

Intracellular drug levels will be correlated with pill count and self report data for those volunteers reporting drug use in the past 48 hours. Levels of drug in hair samples will be evaluated for exploratory purposes only.

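### Section 14.2.4 tests the primary adherence versus intracellular drug level relationship with no regimen term, although the synopsis correlates it within each regimen; one test across both FTC/TDF arms can be confounded by regimen.

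*Protocol*

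**What the plan says.** Section 5.1.1 lists the endpoint as primary, without grouping by regimen: "The relationship between intracellular drug levels and adherence in volunteers assigned to FTC/TDF". The synopsis adds the grouping: "Intracellular drug levels will be correlated with adherence data for volunteers assigned to FTC/TDF for each regimen". The background (section 3.3.3.2) has the same aim, to learn how far "drug levels are associated with objectively measured adherence both for daily PrEP and for intermittent PrEP".

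Section 14.2.4, which specifies the tests, does not mention grouping. It says "The relationship between adherence and intracellular drug level will be evaluated in the volunteers assigned to active regimens FTC/TDF" and then "The correlation between mean adherence execution over the prior month and intracellular drug level will be tested using Pearson's correlation coefficient". A t test of mean level at 90% adherence or more against less than 90% follows. Neither test is stratified or adjusted for regimen, and the text does not say that the regimens are combined.

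Section 14.2.5 plans a separate correlation with other adherence measures in a subset: "Intracellular drug levels will be correlated with pill count and self report data for those volunteers reporting drug use in the past 48 hours". Its standing relative to the primary endpoint is not stated.

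**The concern.** Execution in section 14.2.4 is MEMS events divided by expected doses. Full execution means 7 tablets a week on daily dosing, but 2 plus any post-coital doses on the intermittent regimen. Equal percentages therefore correspond to different drug intake, and section 14.2.5 itself considers that level may fall on intermittent dosing. If adherence also differs between regimens, one correlation across both arms mixes the regimen contrast with the relation of interest.

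The t test has the same problem and does not name its adherence scale. On the adherent-day scale that 14.2.4 defines for intermittent volunteers, someone with no tablets and no reported sex still scores 5/7 = 71%. A daily volunteer with no tablets has 0% execution.

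The aim is to learn whether drug level can stand in for adherence in later studies. A regimen artefact could hide that relation or imitate it.

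**Working it through.** The protocol states no expected correlation or power for this analysis, so there is no figure to reproduce.

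**Inputs from the protocol**
- Arm sizes (section 5.2.2): "24 FTC/TDF daily, 24 FTC/TDF intermittent, 12 placebo daily, 12 placebo intermittent recipients", so 24 per active regimen and 48 combined.
- Within-arm SD of natural-log level: 1.0 or 0.5 (section 14.2.5).
- Regimen difference in level: two-fold, ln 2 = 0.693. Section 14.2.5 uses this as a difference to rule out; here it is an illustration.

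**Assumptions**
- Two-sided 0.05. None is stated for the correlation; it is borrowed from "a two-sided, 0.05 level binomial test of 75% adherence" in 14.2.4.
- Mean adherence equal in the two regimens, or 1 within-arm SD apart in either direction.
- Level analysed on the log scale.

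**Formula.** Let da and dc be the daily-minus-intermittent differences in adherence and log level, in within-arm SDs. With equal arms,

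r_pooled = (r_within + da·dc/4) / sqrt[(1 + da²/4)(1 + dc²/4)].

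For SD 1.0, dc = 0.693; for SD 0.5, dc = 1.386. When |da| = 1, |da·dc|/4 is 0.173 or 0.347, and the denominator is sqrt(1.25 × 1.120) = 1.183 or sqrt(1.25 × 1.480) = 1.360.

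| SD | Intermittent adherence | r_within 0 becomes | null significant | r_within 0.30 becomes |
|---|---|---|---|---|
| 1.0 | equal | 0 | 5% | 0.30/1.058 = 0.28 |
| 1.0 | 1 SD lower | +0.15 | 17% | 0.473/1.183 = 0.40 |
| 1.0 | 1 SD higher | -0.15 | 17% | 0.127/1.183 = 0.11 |
| 0.5 | equal | 0 | 5% | 0.30/1.217 = 0.25 |
| 0.5 | 1 SD lower | +0.25 | 42% | 0.647/1.360 = 0.48 |
| 0.5 | 1 SD higher | -0.25 | 42% | -0.047/1.360 = -0.03 |

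The significance column uses Fisher's z at n = 48. For SD 0.5, atanh(0.255) × sqrt(45) = 1.75 and Φ(1.75 - 1.96) = 0.42. For SD 1.0, atanh(0.146) × sqrt(45) = 0.99 and Φ(0.99 - 1.96) = 0.17. Simulation with 20,000 replicates per scenario gave about 43% and 17%. In the last row, both within-regimen correlations were positive and the pooled one negative in 49% of replicates.

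**Power of the alternatives**
- Per regimen, n = 24 (critical |r| 0.404). At r = 0.30, 0.3095 × sqrt(21) = 1.42, giving 29%. At r = 0.35, 0.3654 × sqrt(21) = 1.67, giving 39%.
- Regimen-adjusted, n = 48, one covariate. At r = 0.30, 0.3095 × sqrt(44) = 2.05, giving 54%. At r = 0.35, 0.3654 × sqrt(44) = 2.42, giving 68%.

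**The 48-hour subset in 14.2.5.** Monday and Friday doses leave gaps of 96 and 72 hours. A fully adherent intermittent volunteer with no post-coital dose is more than 48 hours from the last dose for 48 + 24 = 72 of 168 hours a week (43%). A fully adherent daily volunteer never is. Sections 3.3.3.2 and 9.4 tie 48 hours to tenofovir detectability in plasma, whereas 3.3.3.2 puts the intracellular half-life of tenofovir diphosphate at 60 hours or more. The restriction thus removes low adherers in both arms, and some fully adherent volunteers in one arm only.

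**The case against.** Section 14.2.4 never says the regimens are pooled. The same section says so openly where it combines active and placebo groups, the synopsis supplies the missing grouping, and an analysis plan not shown here may settle it. That stands in part: 14.2.4 is silent, and pooling is a reading of it. But the section that specifies the tests names one correlation and one t test for a primary endpoint, so the protocol leaves room for two analyses that can disagree.

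Some stronger readings are not supported:
- A reader might count three competing definitions. The 14.2.5 correlation uses pill count and self-report, and nothing there restricts or replaces the MEMS analysis.
- A reader might infer that the sign depends on which text is followed. Reversal requires adherence and level to differ between regimens in opposite directions, with |da·dc|/4 larger than r_within.
- A reader might take the 68% power at r = 0.35 as the synopsis analysis. It belongs to an adjusted analysis of all 48; each per-regimen test has 39%.

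Per-regimen testing also has a price: at r = 0.30, power is 29%, against 55% at n = 48 if regimen made no difference. The pharmacokinetic modelling in 14.2.5, which uses actual dosing records, means the surrogate question does not rest on this correlation alone. That limits the consequence but does not resolve the mismatch.

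**Conclusion.** The concern holds as a mismatch on a primary endpoint: a within-regimen correlation in the synopsis, and tests with no regimen term in 14.2.4. If 14.2.4 is run across both active arms, the harm ranges from small with equal mean adherence to material with adherence 1 SD apart, as tabulated. The larger effects rest on the assumed two-fold level difference and adherence gap; the protocol predicts neither, nor the direction of any gap. The 48-hour restriction is a smaller, separate weakness: it truncates adherence and excludes volunteers unequally by regimen. The 43% is a share of hours in the week; the share of visits affected depends on their day and on post-coital dosing.

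**What to change.** In section 14.2.4, report the MEMS-execution correlation within each regimen, as in the synopsis. If a single test is wanted, regress log level on adherence with a regimen term in all 48 volunteers, because the per-regimen tests alone have low power. Stratify or adjust the 90% comparison by regimen in the same way, and name its adherence scale.

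In section 14.2.5, label the pill-count and self-report correlation as supportive, run it by regimen in all FTC/TDF volunteers with a level, and keep the 48-hour subset as a sensitivity analysis.

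The cost is a change of wording in two sections and one degree of freedom for regimen in the combined model. No new data, samples or visits are needed.

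### Section 14.2.4 names Pearson's correlation and a t test for intracellular drug level without a log scale, although 14.2.5 assumes that variable is log-normal; read plainly, this costs power

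*Protocol*

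**What the plan says.** Section 14.2.4 names two tests of adherence against intracellular level in volunteers assigned to FTC/TDF. The first: "The correlation between mean adherence execution over the prior month and intracellular drug level will be tested using" Pearson's coefficient. The second: "Mean drug levels in individuals with" 90% or higher "adherence will be compared with those with <90% adherence using a student's T test". Neither sentence mentions a logarithm, a geometric mean or a rank method.

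Section 14.2.5, which follows directly, treats the same variable differently: "Assuming Week 16 intracellular drug concentration has a log-normal distribution with a between subject standard deviation of 1.0 on the natural logarithm scale". Its power statements are about ratios of geometric means: "this study should have about 79% power to rule-out a two-fold or greater relative decrease in the geometric mean concentration", and "If the between subject standard deviation is 0.5, then there will be about 80% power to rule-out a 1.5-fold or greater decrease".

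The relationship between adherence and intracellular level is a primary objective (section 4.1) and is listed among the primary endpoints (section 5.1.1, Adherence). The Synopsis says the correlation is done for each regimen, so its planned sample is 24. Section 14.2.4 does not say whether the t test pools the two active regimens (48) or is run within each.

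**The concern.** If the concentration is log-normal, its standard deviation on the original scale is proportional to its mean. Groups with different means then have different variances, and a few high values carry much of the weight in an arithmetic mean or a Pearson coefficient. The log scale removes both problems, and 14.2.5 already uses it.

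At stake is the sensitivity of a listed primary analysis. Section 14.2.4 hopes that it may provide adherence estimates for later studies without detailed objective measures. A real relationship could be missed on the original scale that the same data would show on the log scale. An analysis plan that followed 14.2.4 to the letter would carry the mismatch forward.

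**Working it through.** **Inputs from the protocol.** 24 volunteers on daily and 24 on intermittent FTC/TDF (section 14.1); log-normal concentration with log SD 1.0 or 0.5, paired with a two-fold or 1.5-fold difference (section 14.2.5).

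**Assumptions, not in the protocol.** Two-sided 0.05, since no level is given for these two tests; the numbers at or above and below 90% adherence; a log-linear relation with slope 3; and adherence distributed as Beta(6, 1.5).

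**The plan's own figures.** With 24 per group, power is Φ(ln(fold) / (SD × √(2/24)) − z).

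- SD 1.0, two-fold: 0.693 / 0.2887 = 2.401. This gives 77.5% with z = 1.645 and 67.0% with z = 1.960. The protocol states about 79%.
- SD 0.5, 1.5-fold: 0.405 / 0.1443 = 2.809. This gives 80.2% with z = 1.960 and 87.8% with z = 1.645. The protocol states about 80%.

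Both figures are recovered to within about two points on the log scale, so 14.2.5 does work there. They match at different significance levels (one-sided 0.05 for the first, two-sided for the second), which is a separate matter.

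**Size of the skew.** The coefficient of variation of a log-normal is √(exp(SD²) − 1): √(2.718 − 1) = 1.31 at SD 1.0, and √(1.284 − 1) = 0.53 at SD 0.5. A two-fold difference in means implies a 2² = 4-fold ratio of variances; a 1.5-fold difference implies 1.5² = 2.25. Student's pooled t test handles this worst when the group with the larger variance is also the larger group, that is, when most volunteers are high adherers.

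**t test, 48 volunteers, simulated power (20,000 to 40,000 runs per setting).**

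| High / low adherers | SD 1.0, two-fold: raw | log | SD 0.5, 1.5-fold: raw | log |
|---|---|---|---|---|
| 24 / 24 | 47% | 65% | 74% | 79% |
| 34 / 14 | 27% | 57% | 61% | 71% |
| 38 / 10 | 15% | 48% | 47% | 61% |
| 14 / 34 | 50% | 57% | 70% | 71% |
| 12 / 36 | 49% | 53% | 66% | 66% |

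Within one regimen at SD 1.0 and two-fold, a 12/12 split gives 24% raw against 37% log, and 16 high with 8 low gives 13% against 34%.

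**Pearson's test, Beta(6, 1.5) adherence, log slope 3.**

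| n | SD 1.0: raw | log | SD 0.5: raw | log |
|---|---|---|---|---|
| 24 | 22% | 46% | 86% | 93% |
| 48 | 47% | 77% | 99% | over 99% |

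A second set of assumptions, fixing the log-scale correlation at 0.5 with n=24, agrees in direction. At SD 1.0, power falls from 73% to 58% with normally distributed adherence and from 72% to 46% with Beta(8, 2) adherence. At SD 0.5 it falls from 73% to 69% and from 72% to 64%.

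**Type I error on the raw scale.** With no true difference or correlation, the t test rejects in about 3.5% to 5% of runs and Pearson's test in about 5%.

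**The case against.** Section 14.2.4 never says that the concentrations are untransformed. The next section declares the variable log-normal, and the Synopsis and section 13.3 leave the full analysis to a plan agreed before unblinding, which may well set the scale. This stands in part: the raw scale is an inference. It is the natural one, because the authors wrote geometric mean in 14.2.5 and plain mean in 14.2.4. The protocol also does not leave the method open here; it names the tests.

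The size of the loss depends on how many volunteers reach 90% adherence, which nobody knows in advance. Section 3.3.3.1 cites trials in which 50% took more than 90% and 81% took at least 90% of study drug. Losses near 30 points need most volunteers to be high adherers and log SD 1.0. The Beta(6, 1.5) used for the correlation puts only 27% at or above 90%, which corresponds to about 13 of 48. With a split close to that (14/34), the t test loses only about 7 points at SD 1.0. The t-test and correlation results are therefore separate illustrations and do not form one joint scenario. This objection stands in full.

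A reader might go further and infer that these analyses lose much of their power whatever the data, that they risk false findings, or that they alone decide whether drug level can stand in for adherence. The documents do not support any of these. Section 14.2.5 also allows log SD 0.5, where the loss is modest or absent; type I error is not inflated; and 14.2.4 and 14.2.5 include other comparisons of MEMS data with drug levels, including pharmacokinetic simulation.

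**Conclusion.** The point holds as an inconsistency of scale with a cost in power. Sections 14.2.4 and 14.2.5 treat one variable in two ways, and the plain reading of 14.2.4 is the less powerful. At log SD 1.0 and a two-fold difference, the t test loses from about 4 points (12 high/36 low) to about 33 points (38/10), with 18 points at an even split; Pearson's test loses about 24 points at n=24 and 30 at n=48. At log SD 0.5 and a 1.5-fold difference, the t-test loss runs from none to about 14 points, and Pearson's test at n=24 loses about 7. In every setting examined, the log scale did at least as well under the protocol's own distributional assumption.

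These sizes rest on the assumed splits, slope, adherence distribution and two-sided 0.05 level, and on reading 14.2.4 as untransformed. The change is worth making because the endpoint is listed as primary and the cost is small.

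**What to change.** In section 14.2.4, state that both analyses use log-transformed intracellular concentration: Pearson's correlation of adherence with log level, and the t test on log level with the result reported as a geometric mean ratio and its 95% CI. That agrees with 14.2.5. Keep the correlation by regimen, as the Synopsis already has it.

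The cost is a sentence or two, with no extra volunteers or samples. There is one small downside. Values below the assay limit need a rule fixed before unblinding, because non-adherent volunteers may have undetectable levels, and the log value imputed for them is influential at the low-adherence end. A Spearman correlation would serve as a sensitivity check. At n=24 with a log-scale correlation of 0.5, its simulated power is 64% to 67% at either SD.

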treatment assignments are unblinded, samples from volunteers assigned to FTC/TDF will be tested for intracellular drug levels. The relationship between adherence pattern and intracellular drug level will be explored to see if these drug levels could be used as a proxy for adherence in future studies. Similarly, hair samples will be collected from all volunteers, tested for drug levels in volunteers assigned to FTC/TDF and correlated with adherence patterns. Hair collection will take place at the time points indicated in Appendix A1.

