#### **14.2.4 Adherence**

The mean, median and range of adherence to PrEP will be determined using MEMS data for volunteers. Previous work has shown that the accuracy of MEMS assessment can be improved with a 3-day structured self-report of the number of extra cap openings and the number of times multiple doses are taken out of the bottle [119]. The *adjusted MEMS adherence* is calculated by the interview adjusted number of bottle openings/number of doses prescribed over the prior three days. The *unadjusted MEMS* measure is the number of electronically recorded bottle openings divided by the number of expected doses based on IVR sexual activity data, since the last interview[48]. MEMS adherence will be classified by the schema proposed by Vrijens where adherence is organized in terms of persistence and execution [161,162]. Persistence is time to treatment discontinuation. Treatment discontinuation will be defined as the first day of 30 consecutive days without a MEMS cap event. Treatment execution is defined as the number of MEMS caps events divided by the number of expected doses prior to treatment discontinuation. We also will use MEMS to characterize treatment interruptions and whether patterns of adherence are temporally related to sexual behavior. These approaches have been successfully piloted in Uganda [77,94].

For volunteers assigned to intermittent regimens, a combination of MEMS and IVR/SMS data will be used. Each day will be classified as an adherent or nonadherent day. Adherent days will be defined as: any day on which sexual activity was reported and a MEMS event occurred, any Monday or Friday on which a MEMS event occurred, and any other day of the week on which neither sexual activity nor a MEMS event occurred. Adherence will be calculated as the number of adherent days since the last visit divided by the number of days since the last visit.

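### The Pearson correlation of intracellular drug level with adherence uses execution, which stops counting at discontinuation, so volunteers who have stopped dosing drop out of the test or are scored on their pre-stop days only

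*Protocol*

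**What the plan says.** Section 5.1.1 lists, among the primary adherence endpoints, "The relationship between intracellular drug levels and adherence in volunteers assigned to FTC/TDF". Section 14.2.4 gives the purpose: knowing this relationship "may provide adherence estimates for future studies which do not include detailed objective adherence measures".

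Section 14.2.4 splits MEMS adherence into persistence and execution:

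- "Treatment execution is defined as the number of MEMS caps events divided by the number of expected doses prior to treatment discontinuation".
- "Treatment discontinuation will be defined as the first day of 30 consecutive days without a MEMS cap event". The stop is thus dated back to the start of the gap.
- Later in the section, non-persistence is "defined by >30 days without a MEMS event", a slightly different threshold.

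The variable tested against drug level by Pearson's coefficient is then fixed: the test is of the "correlation between mean adherence execution over the prior month and intracellular drug level".

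Section 9.4 says whose levels are measured: after unblinding, "samples from volunteers assigned to FTC/TDF will be tested for intracellular drug levels". It does not limit this to volunteers who are still dosing. Nothing in the protocol says what value a discontinued volunteer takes in the correlation.

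**The concern.** If drug level is to stand in for adherence in later studies, the test has to include people who are not taking the drug. They anchor the bottom of both scales. Execution describes how well people dose while they are still dosing, and by definition it says nothing about the time after a stop. Used as the adherence variable, it leaves out volunteers who have a sample and whose recent adherence is known to be zero, or it credits them with good dosing from before the stop. A real relationship can then look weaker than it is. Because the protocol names and defines the variable, this is a stated rule that works badly, not a detail left open for the SAP.

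**Working it through.** The protocol states no expected correlation, power or sample size for this test, so there is no figure to reproduce.

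**Inputs from the protocol.** The definitions are those above. The intracellular half-life of tenofovir diphosphate is at least 60 h (section 3.3.3.2). The between-subject SD of the natural-log level is 1.0, or alternatively 0.5 (section 14.2.5). Dispensing is about every 4 weeks (section 8.4), so the prior month is taken as 28 days. There are 24 volunteers per FTC/TDF regimen.

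**Step 1: worked histories.** Daily regimen, perfect dosing before the stop, days numbered from 0.

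- Execution = openings ÷ expected doses in the window that fall before the stop.
- All-days adherence = openings ÷ 28.
- Level relative to steady state ≈ 0.5^(24 × days off ÷ 60).

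| Stop day | Draw | Execution | All-days adherence | Level |
|---|---|---|---|---|
| 28 | Week 8 (day 56) | 0/0 | 0/28 = 0% | 0.5^11.2 = 0.04% |
| 38 | Week 8 | 10/10 = 100% | 10/28 = 36% | 0.5^7.2 = 0.7% |
| 70 | Week 12 (day 84) | 14/14 = 100% | 14/28 = 50% | 0.5^5.6 = 2.1% |
| 82 | Week 16 (day 112) | 0/0 | 0% | 0.5^12 = 0.02% |
| 83 | Week 16 | 0/28 = 0% | 0% | 0.03% |
| 94 | Week 16 | 10/28 = 36% | 36% | 0.7% |

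At Weeks 8 and 12 both faults occur. At Week 16 only drop-out occurs: MEMS data end there, so a stop inside the last 28 days leaves a gap shorter than 30 days, is not flagged, and is scored correctly. The stops on days 82 and 83 show how arbitrary the cut is. Neither volunteer dosed in the prior month, yet one is excluded (a gap of 112 − 82 = 30 days) and the other scores 0% (29 days). Under the more-than-30-days wording the first would not be flagged either.

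**Step 2: illustration of size.** Simulation at Week 16, n = 24, daily dosing, 60 h half-life. The following are assumptions that the protocol does not give: mean adherence 88% with a Beta spread, 2 volunteers who stop silently between days 20 and 79 but still give samples, and levels floored at 2% of steady state. There were 1,500 replicates per setting. Every such stopper has execution 0/0.

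| Mean coefficient | Stoppers scored 0% | Stoppers dropped |
|---|---|---|
| Pearson, untransformed, SD 0.5 | 0.52 | 0.22 |
| Pearson, untransformed, SD 1.0 | 0.28 | 0.10 |
| Pearson, log level, SD 0.5 | 0.87 | 0.26 |
| Pearson, log level, SD 1.0 | 0.69 | 0.14 |
| Rank correlation, SD 0.5 | 0.40 | 0.22 |
| Rank correlation, SD 1.0 | 0.32 | 0.12 |

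On the untransformed scale, power at 0.05 is about 92% against 14% (SD 0.5) and 10% against 5% (SD 1.0).

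**Step 3: a different model.** Adherence was drawn from Beta(8,2), 20% of volunteers stopped at a uniformly random time, and the level was left untransformed. All-days adherence against execution as defined gives mean r of 0.59 against 0.26 (SD 0.5) and 0.36 against 0.14 (SD 1.0) at Week 12. At Week 16 it gives 0.64 against 0.43 and 0.40 against 0.23. With no stopping the two scorings are identical.

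**The case against.** **Other analyses cover the endpoint.** Section 14.2.4 also plans a general comparison of MEMS adherence with drug levels and a t test of levels at 90% adherence or more against less. Section 14.2.5 compares concentrations simulated from MEMS data with observed ones. None is stated to use execution. This stands: a reader might infer that the whole primary endpoint is compromised, but the documents support that only for the Pearson test.

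**The size depends on the model.** Section 14.2.4 does not state a log transform; the log-normal assumption in section 14.2.5 supports the geometric-mean comparison. A reader might infer from the log-scale results that power falls from near certainty to very little. That is not supported in general: on the untransformed scale at SD 1.0, power is low under either scoring. The large coefficients also rest on two influential points, and the rank correlation shows a smaller contrast. The number of silent stoppers who still give samples is assumed, and stops late in follow-up are not flagged at all.

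**Pre-stop adherence carried to Week 16.** A reader might infer that volunteers who stopped long before Week 16 keep their earlier high adherence. That would require ignoring the limit to the prior month. The mismatch arises only at earlier visits, when the stop falls inside the month, and the pre-stop value is high only if dosing was good until then.

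**Regimen.** The illustration covers daily dosing. For intermittent volunteers the protocol also defines adherence as adherent days over all days between visits, without truncation, and does not say how that relates to execution. The size is therefore not shown for that regimen.

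**Execution is a recognised concept, and 0/0 is SAP detail.** Separating execution from persistence is legitimate, and persistence has its own Kaplan-Meier analysis. But the protocol has chosen execution for this test. It could be read as letting the prior-month window override the truncation, which would score stoppers 0%, but the text does not say so.

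**Conclusion.** The point holds in a limited form. Followed as written, the Pearson test excludes volunteers whose whole prior month lies after a stop of 30 days or more. At visits before Week 16 it scores those who stopped inside the month on pre-stop days only. Both effects follow from the protocol's definitions without any modelling.

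The direction was the same in every setting with flagged stops: the coefficient is lower with execution than with all-days adherence. The size depends on the assumed stopping rate, the spread of adherence, the visit and the scale of the level. The untransformed results are closest to the test as written. The defect is confined to this one test and vanishes if nobody stops. It should be corrected because the relationship is a primary endpoint meant to support a proxy for adherence.

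**What to change.** In section 14.2.4, define the adherence variable for this correlation as MEMS doses taken divided by expected doses over the fixed 28 days before the draw, for every FTC/TDF volunteer with a sample. Count expected doses after a stop as missed, which gives 0% when the whole window follows the stop. Keep execution among persisters as a secondary analysis.

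Report a rank correlation beside Pearson's. Stopped volunteers become influential points under the new scoring; this is its small downside.

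State that the 90% split uses the same all-days variable, and reconcile the two thresholds for discontinuation (30 consecutive days against more than 30).

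The cost is a few sentences of text and no new data.
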